### Cost-effectiveness

Cost-effectiveness analysis will be conducted from a societal perspective before, during, and after treatment. The incremental cost-effective ratio will be calculated. Differences between the two intervention groups (control group and intervention group) in direct medical expenses related to the internet-based program include the time spent logged into the program for participants and therapists, the time that participants spend engaging in the activities recommended by the program, and the costs associated with data server maintenance and data storage. The value of the time spent in the program will be calculated by multiplying the time estimates by the median hourly wage of the therapists or of a population similar to the program participants. Time absent from work and contact with psychiatric, social, or general medical services will also be considered. Market values will be considered for this analysis.

Other expenses, such as those relating to the development of the internet application, programming costs, (psychoeducational) content development, and chat software are considered ‘sunk costs’ and will not be included in the analyses because they are not expected to recur with dissemination of the program.

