#### The self-help manual

The self-help manual includes an initial chapter that provides general information on obesity and bariatric surgery followed by 12 different psychoeducational and CBT-based chapters. A new chapter will be available each month. Participants can choose the chapter that best fits their needs each month. There is no pre-established sequence of chapters, as each chapter addresses different skills that do not rely on previous knowledge. One exception is the first chapter, which is the same for every participant, given its motivational nature. To complete the chapter successfully, participants must submit information on the respective tasks. Completed chapters remain open for future consultation. Tangible lifestyle changes that will be practiced during intervention will be:Having regular and planned eating patterns;Have a daily protein intake between 60 g and 80 g.Achieve at least 150 min/week of structured physical activity plus 5000–7499 steps per day; or take at least between 7500–9999 steps per day.Having systematic self-monitoring strategies.

Table 1 presents the title and objectives of each chapter of the self-help manual. Further information regarding the contents of this self-help manual can be provided by the authors on request, for research and replication purposes.

**Table 1 Tab1:** Chapter from the self-help manual component of APOLO-Bari

Chapter	Objectives	Description and lifestyle changes
General information: *obesity* and *bariatric surgery* Note: Provided in the open area of the homepage. All study participants will have access to this chapter after registering.	To educate about obesity and bariatric surgery as a long-term intervention treatment.	Different procedures and their post-surgery implications; Obesity, psychosocial impairments and maintenance mechanisms; The role of bariatric surgery as a weight loss treatment for obesity.
*Motivation for intervention and importance of monitoring weight*	To highlight individual responsibility and the need for long-term lifestyle modifications; To educate about self-monitoring and regular self-weighing.	How to use the program; The top ten recommendations of your bariatric surgeon; How weight varies after surgery and in the long term; Why and how to control your weight.

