### Informed consent and randomization

Those who agree to participate in the study will have a computer connected to the internet, and each participant will complete the informed consent form online and register in the program by creating a personal username and password. All participants will complete an initial short sociodemographic and clinical questionnaire (see details in the measures section). To ensure concealment of allocation, the APOLO-Bari system will then automatically randomize (computer-generating random numbers) the participants on a 1:1 basis, matching for age, sex, and surgery type.

After randomization, intervention group members will receive full access to the three components of the APOLO-Bari program in their personal accounts. The intervention will last for 12 months, and a 6-month period will follow, with no program access possible. During the intervention period, the system will record data on log-in frequency, task submission, and weekly monitoring from the intervention group.

The control group will only have access to general information on obesity and bariatric surgery and to the set of self-report measures at the different assessment times. The control group participants will be informed of the assessment times and the possibility of accessing the full program after the study is complete. Both groups will receive reminder emails every time a questionnaire or activity is available.

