### Weekly assessment

The weekly assessment includes three questions that will provide information for the feedback message and six other questions designed to monitor the relevant behaviors for this population. For the feedback message, the participants respond to the number of days in the previous week that they engaged in grazing, binge eating, or overeating. Definitions are provided based on the definitions proposed by Conceição et al. [12] for grazing, and by Fairburn et al. [39] for overeating eating and binge eating episodes. Other questions involve additional eating behaviors (e.g., skipping meals, the level of control over eating) and active or sedentary behaviors. Table 4 presents a list of the items used in the weekly assessment.

**Table 4 Tab4:** Weekly assessment questionnaire for the feedback messaging system

Please respond to the following questions by referring to the previous week (7 days). During the past week…
1. How many days did you skip meals (for example, breakfast, morning snack, lunch)?
2. How many days did you graze or nibble on small or modest amounts of food throughout the day in a repetitive and unplanned manner?
3. How many days did you feel that you overate (for example, had a second helping, continued eating after satiation, overate without feeling hungry)?
4. How many days did you feel that you overate or could not resist eating because you were feeling anxious, nervous, or sad, or other emotions?
5. How many days did you feel that you lost control over what you were eating (for example, being unable to resist eating or to stop eating after you started)
a. On a scale from 1 to 5 (with 1 indicating very low and 5 indicating an extreme loss of control), to what extent did you feel a sense of loss of control during those situations?
6. How many days did you eat compulsively, losing control while eating an amount of food that was extremely large given the situation (for example, twice or more than what others would eat under the same situation)?
a. On a scale from 1 to 5 (with 1 representing very low and 5 representing an extreme loss of control), to what extent did you feel a sense of loss of control during those situations?
7. How many days did you walk for more than 15 minutes?
8. How many days were you involved in structured physical activity for more than 30 minutes, such as going to the gym, playing soccer, or swimming?

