9. On average, how many hours per day did you spend sitting for any reason (for example, working, browsing the internet, driving, watching TV on the sofa)?
10. Did you have surgery to remove the extra hanging skin this week? Yes, Date__; No.

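### The weekly form counts days of activity above a threshold, so neither the activity time to be costed nor the outcome in hours of physical activity can be derived from it without outside assumptions

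*Protocol article*

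**What the plan says.** The Cost-effectiveness section of the protocol article lists, among the between-group differences to be costed, "the time spent logged into the program for participants and therapists" and "the time that participants spend engaging in the activities recommended by the program". Both are valued by "multiplying the time estimates by the median hourly wage of the therapists or of a population similar to the program participants", so both must be expressed as durations.

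Under Primary and secondary outcome measures, one secondary outcome is the number of hours of sedentary and of physical activity, with a recall period of one month.

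The instrument is printed item by item in Table 4 (Weekly assessment). It asks about the past 7 days. Item 7 is "How many days did you walk for more than 15 minutes" and item 8 is "How many days were you involved in structured physical activity for more than 30 minutes". Item 9, "On average, how many hours per day did you spend sitting for any reason", is the only item in hours, and it concerns sedentary time.

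Table 3 shows who completes the form and when. The intervention group answers weekly, the control group at baseline, months 4 and 8 and end of treatment, and both groups at the 6- and 12-month follow-ups. It lists no other measure of activity.

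On programme use, the section Informed consent and randomization says that "the system will record data on log-in frequency, task submission, and weekly monitoring from the intervention group". The section on chat sessions has the psychologist online for 30 minutes per session and lets a participant book one every other week.

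**The concern.** Two planned quantities need a duration of physical activity, and the form supplies a count of days above a cut-off. A day count has no upper limit on minutes, so the same answer covers very different amounts of time.

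The cost analysis needs more than a level. It needs the difference between arms, because controls exercise too. If session lengths differ between arms, a comparison of day counts can mislead about the size of that difference and even its direction.

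At stake are the activity-time input to the incremental cost-effectiveness ratio, if exercise counts as a recommended activity, and the physical-activity outcome in hours whatever the answer to that question. With the form as printed, both would rest on a minutes-per-day figure that the article does not give.

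**Working it through.** The plan states no figure to reproduce. The check compares what is needed with what is recorded, then asks how far the recorded items pin down a duration.

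**1. Needed against recorded**

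| Quantity needed | Unit needed | Named measure | Unit recorded |
|---|---|---|---|
| Time on recommended activities, if this includes exercise | time, by arm | Table 4, items 7 and 8 | days in past 7 above 15 or 30 min |
| Physical-activity outcome | hours, past month | Table 4, items 7 and 8 | days in past 7 above 15 or 30 min |
| Sedentary outcome | hours, past month | Table 4, item 9 | hours per day, past 7 days |
| Participant time logged in | time | log-in frequency | count |
| Psychologist chat time | time | sessions of fixed length | 30 min each |

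The sedentary outcome has the right kind of unit and differs only in recall period. The physical-activity outcome differs in both unit and recall period.

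**2. What one answer to item 8 allows**

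Weekly minutes = days × minutes per day, with minutes per day above 30 and otherwise free.

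- 3 days at 31 min: 3 × 31 = 93 min.
- 3 days at 60 min: 3 × 60 = 180 min.
- 5 days at 31 min: 5 × 31 = 155 min.

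The first two give the same answer with nearly twofold different time. The last two show a possible reversal: 3 days can mean 180 − 155 = 25 minutes more than 5 days.

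**3. The same over a year**

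Hours per year = 52 × days per week × minutes per day / 60. For 5 days a week, with assumed session lengths:

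- 30 min (the floor): 52 × 5 × 30 / 60 = 130 h.
- 60 min: 52 × 5 × 60 / 60 = 260 h.
- 90 min: 52 × 5 × 90 / 60 = 390 h.

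The range is threefold for an unchanged answer. Cost is hours times wage, so for these participants the cost of activity time also spans a factor of three at any wage.

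**4. Log-in time**

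For 52 weekly log-ins at an assumed 5, 15 or 30 minutes:

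- 52 × 5 / 60 = 4.3 h.
- 52 × 15 / 60 = 13 h.
- 52 × 30 / 60 = 26 h.

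The range is sixfold if only a count is kept. It disappears if the server keeps session times.

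**5. Chat time**

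One session every other week is about 26 a year, so at most 26 × 0.5 = 13 h per participant. This needs only the number of sessions held.

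**The case against.** The strongest reply is that this is an article, not the full protocol. It shows no instrument for work absence or service contacts either, although both are costed, so it apparently does not list its resource-use measures. The list of recorded usage data is not said to be complete, and the cost section speaks of time estimates, which need not be individual measurements. For log-in time this reply largely stands: session times may well be stored, and a sentence naming the source is all that can be asked. It does not reach the activity items. Those are printed in full, Table 3 shows no other activity measure, and the mismatch with an outcome in hours lies within the article itself.

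A second reply is that recommended activities are not defined and may mean manual tasks rather than exercise. That stands as a condition on the costing part. It does not affect the physical-activity outcome.

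Two stronger readings are tempting. A reader might infer that the programme's time cost cannot be computed at all. The article does not support this: chat time can be computed from the fixed session length, server costs need no participant form, and estimates from assumed minutes would be consistent with the text.

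A reader might also take the manual's target, "Achieve at least 150 min/week of structured physical activity plus 5000–7499 steps per day", compute 150 × 52 / 60 = 130 hours a year, and conclude that activity time dominates the cost ratio. That figure is gross, whereas the cost needed is the difference from controls. The target has an alternative in steps alone, and the figure presumes that exercise is what the cost section means. It is at most an illustration under one reading and gives no incremental cost.

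**Conclusion.** The point holds for activity time. The named items do not yield hours of physical activity, or the between-arm difference in hours, unless a minutes-per-day figure is brought in from outside. The uncertainty is nearly twofold for a single answer of 3 days (93 against 180 minutes) and threefold for 5 days a week over a year (130 to 390 hours). The session lengths of 31, 60 and 90 minutes are assumptions; only the 30-minute threshold comes from the form.

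For log-in time, all that is missing is a stated source. For psychologist chat time there is no gap. No size can be put on the effect on the cost-effectiveness ratio, because the article gives no between-arm difference in activity, no wage and no definition of recommended activities.

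The impact is confined to the secondary cost-effectiveness aim and the physical-activity outcome. The primary efficacy analysis is unaffected. The change is worth making because it is cheap and recruitment is not complete.

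**What to change.** 1. **Table 4, items 7 and 8.** Add a question on total minutes in the past 7 days to each item, and keep the day counts so that earlier and later answers remain comparable.
2. **Primary and secondary outcome measures.** Reconcile the unit and recall period of the physical-activity outcome with the form. Align the recall period of the sedentary outcome with item 9 as well.
3. **Cost-effectiveness.** Say whether exercise counts as a recommended activity. If it does, cost it as the between-arm difference in minutes at the assessments where both arms have data under Table 3. State which weekly form from the intervention group is matched to each control assessment during the intervention year. Give a sensitivity range over assumed minutes per day for participants who answered the old wording.
4. **Log-in time.** Name the source, for example session time stamps, or give the assumed minutes with a range. Chat time can stay at 30 minutes per session held.

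The cost is two extra questions on an existing form and a few sentences in the text. The downside is that participants already enrolled will have only day counts for their earlier assessments, which the sensitivity range in step 3 is meant to cover.

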### Blinding and data access

Intervention and assessment are conducted exclusively in the APOLO-Bari program. The psychologist participating in the interactive chat sessions does not have access to the program information submitted by the participant. The statistician conducting the statistical analysis has not been involved in the implementation of the program. Treatment allocation has not been previously disclosed to the statistician.

Only the principal investigator and the statistician will have access to the final trial dataset. This is stated in the information for the participant sheet submitted to the ethical committee approval.

### Safety aspects and ethical considerations

The study is being conducted in accordance with the latest version of the Declaration of Helsinki. Approval from the ethical committees involved (Ethics Subcommittee for Life and Health Sciences, University of Minho; Ethics Committee for Health, Hospital of Braga; Ethics Committee for Health, Hospital Center of São João) were obtained and can be consulted found on the current controlled trials website for our trial registration number. Any trial modifications or the inclusion of new health centers as partners for data collection will be communicated to the ethical committees involved as well as to the trial registration organization. Participation in the research project is entirely voluntary. Participants are informed that their present or future medical treatment will not be affected by their decision to participate or not participate. Participants are informed that they can withdraw from the research project at any time without providing a reason. Participants are assigned a code number to maintain confidentiality. All personal data are stored and handled according to data protection principles. In practice, this arrangement means that the written material will be stored in secure locations, and data stored on the computer will be password protected and encoded (SSL technology) and regularly backed up. Additionally, any publication derived from the personal data will be presented in a way that ensures it is not possible to identify individuals. Communications via internet chat will be protected through encoding (SSL technology).

Our team also shares concerns regarding the identification (by our research team or internet program) of patients who might be under extreme distress. If so, the program or researcher will generate an alert, and the project coordinator will proceed to refer the patients to additional, more specific care in the medical center. Alerts will be generated if: (a) significant weight regain is experienced (≥10 kg since the beginning of intervention); (b) there are maladaptive eating behaviors for at least 3 months with a frequency of at least once a week. A participant under individual support may continue the program unless otherwise requested by the accompanying specialist.

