The APOLO-Bari components described here are not intended to replace necessary treatment or individual care targeting more complex problems when necessary (e.g., binge eating, bulimia nervosa, depression). Rather, the system enables the systematic monitoring of risk behaviors and refers patients to more intensive care when needed. APOLO-Bari is intended to be an adjunctive intervention to treatment as usual to improve outcomes by preventing weight regain and alerting the research and clinical team of patients who are at increased risk for weight regain. The major program objective is to prevent long-term weight regain through:Providing self-help for the education and training of relevant skills for the postoperative period (self-help manual);Promoting healthy and adaptive eating patterns (feedback messaging system);Ensuring the early detection of risk behaviors (feedback messaging system);Bridging the gap between patients and clinical settings while allowing continuous and direct contact with bariatric surgery specialists (chat sessions);Improving compliance with daily behavioral adjustments (all components involved).

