Furthermore, the server will send a motivational message directly when a participant has missed a weekly assessment or has not logged in for more than a month. The system will automatically send an email (‘case alarm’) to the research team when a participant reports symptoms that require additional clinical attention: (i) weight regain of >5 kg over the previous 3 months and (ii) the presence of any risk behaviors every week for at least 3 months. In such a case, the research team will contact the participant via email.

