### Subjects

Participants (male and female) between 18 and 65 years of age who underwent bariatric surgery (sleeve gastrectomy and gastric bypass) at least 12 months and not more than 20 months previously will be recruited. This timeframe is used to anticipate the period when patients appear to be at risk of weight regain (12–24 months postoperatively) [2] and when they need help coping with lifestyle adjustments.

For the purpose of this study, patients who initially lost weight successfully after surgery will be included. We seek to exclude potential medical or surgical problems that are not related to lifestyle and psychological adjustment and that could be implicated in and limiting to the initial weight loss. Furthermore, given that our ultimate objective is to prevent weight regain, significant initial weight loss is required. Significant weight loss will be considered when the percentage of excessive weight loss is higher than 30. Furthermore, participants who present with significant weight regain (more than 15 % of the total weight loss) since the nadir weight at the time of registration will be excluded. Other specific exclusion criteria include the following:No regular internet access;Inability to read and understand Portuguese instructions;Lack of willingness to have or create an email account;Presence of an active psychiatric disorder (e.g., bipolar disorder, psychotic disorder, suicidal ideation, eating disorders);Intake of weight-affecting drugs;Concomitant weight loss treatment besides treatment as usual;Pregnancy or lactation.

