### Psychological self-report measures

Repetitive Eating Questionnaire [12]: This self-report questionnaire assesses a grazing-type eating pattern through 15 items, resulting in two subscales that reflect compulsive grazing and non-compulsive grazing subtypes.

Depression Anxiety Stress Scales [36]: This 21-item questionnaire generates subscales on depression, anxiety, and stress.

Eating Disorder – 15 [37]: This 15-item questionnaire assesses eating disorder cognition and behaviors, with subscales for weight and shape concerns and for eating concerns.

Negative Urgency Subscale [38]: This 12-item scale assesses an individual’s tendency to surrender to strong impulses, particularly when accompanied by negative emotions, such as depression, anxiety, or anger.

Influence of weight: Developed by the research team, this 12-item measure inquires about the influence of weight in different areas of life (e.g., intimate relationships, professional roles, self-esteem).

Satisfaction questionnaire: Developed by the research team, this 19-item questionnaire addresses the utility and feasibility of the program from the patient’s perspective.

All questionnaires have been used with this sample by the research team in previous studies, and show good internal consistency for use with bariatric surgery patients.

Table 3 presents a summary of the self-report measures used for each group at each assessment time.

**Table 3 Tab3:** Timeline for the self-report measures

	Registration	Baseline (*T* _b_)	4-month midterm assessment (*T* _m4_)	8-month midterm assessment (*T* _m8_)	Final (end of treatment) assessment (*T* _f_)	6-month follow-up assessment (*T* _fu6_)	12-month follow-up assessment (*T* _fu12_)	Weekly
Sociodemographic weight history	X	–	–	–	–	–	–	–
Clinical inventory	–	X	X	X	X	X	X	–
Repetitive Eating Questionnaire [12]	–	X	X	X	X	X	X	–
Depression Anxiety Stress Scales [36]	–	X	X	X	X	X	X	–
Eating Disorder – 15 [37]	–	X	X	X	X	X	X	–
Negative Urgency Subscale [38]	–	X	X	X	X	X	X	–
Influence of weight	–	X	X	X	X	X	X	–
Satisfaction questionnaire	–	–	–	–	Intervention group	–	–	–
Eating and exercise behaviors (Table 4)	–	Control group	Control group	Control group	Control group	X	X	Intervention group

*X* available for both intervention and control group

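### The referral alert set up for patients in extreme distress lists only weight and eating triggers, and no alert is tied to the distress scores collected in both arms

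*Protocol article*

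**What the plan says.** Under Safety aspects and ethical considerations, the protocol article states a concern with the "identification (by our research team or internet program) of patients who might be under extreme distress". Where such a patient is identified, the program or a researcher raises an alert and the project coordinator refers the patient to more specific care at the medical center. The criteria follow: "Alerts will be generated if: (a) significant weight regain is experienced", set at 10 kg or more from the start of the intervention, and (b) "there are maladaptive eating behaviors for at least" 3 months, occurring at least once a week.

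A second mechanism, the case alarm, is described under The weekly feedback monitoring system. It emails the research team "when a participant reports symptoms that require additional clinical attention". Its criteria are a regain of more than 5 kg over 3 months and any of the risk eating behaviors every week for at least 3 months.

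The rationale section says the program does not replace "individual care targeting more complex problems when necessary (e.g., binge eating, bulimia nervosa, depression"), and that the system "refers patients to more intensive care when needed".

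The distress measure is the Depression Anxiety Stress Scales: "This 21-item questionnaire generates subscales on depression, anxiety, and stress". Table 3 schedules it for both arms at baseline, 4 months, 8 months, end of treatment, and 6 and 12 months of follow-up. The clinical inventory, which covers current psychiatric or psychological disorders, has the same schedule.

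**The concern.** The rule is introduced for one condition and triggered by others. Weight regain and disordered eating may accompany distress, but neither measures it. The trial collects a direct measure of depression, anxiety and stress six times in each arm, and the article gives those scores only analytic uses.

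What is at stake is patient safety. The Subjects section lists "Presence of an active psychiatric disorder", with suicidal ideation among the examples, as an exclusion, and this applies at entry. The last assessment falls about 24 months after baseline (12 months of intervention plus 12 of follow-up), so such a condition can emerge during the study. If it does while weight holds and eating stays orderly, the printed triggers do not pick it up, even though the trial may already hold the score that shows it.

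**Working it through.** The point depends on no sample size, power or error rate, so there is no figure of the plan to reproduce. The check sets the alert rules beside the measures and the uses stated for those measures.

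**Step 1: what each alert criterion reads.**

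| Section | Criterion | Reads |
|---|---|---|
| Safety aspects, (a) | Regain of 10 kg or more from start of intervention | Weight |
| Safety aspects, (b) | Maladaptive eating at least weekly for 3 months | Eating |
| Weekly feedback, (i) | Regain of more than 5 kg in 3 months | Weight |
| Weekly feedback, (ii) | Any risk behavior every week for 3 months | Eating |

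Count: 2 weight + 2 eating = 4 criteria. Criteria reading depression, anxiety, stress or suicidality: 0.

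**Step 2: where distress is measured.** Table 3 marks the Depression Anxiety Stress Scales for both groups at T_b, T_m4, T_m8, T_f, T_fu6 and T_fu12, which is six assessments. The clinical inventory is marked at the same six. Assessments at which either instrument is linked to an alert: 0 of 6.

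**Step 3: what the scores are used for.** Primary and secondary outcome measures treats psychological symptoms as secondary outcomes, as midterm predictors of later weight, and as baseline moderators (severity of general psychopathology). Statistics enters the self-report measures, depression and general distress among them, in an analysis of covariance against weight outcomes. Neither section mentions a cut-off, a review of scores during the trial, or a referral.

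**Step 4: whether another route supplies a distress criterion.**
- The rationale section names depression as a problem that may need individual care, but describes referral as following from the monitoring of risk behaviors, so it adds no criterion.
- The safety section allows a researcher to raise an alert. It gives no distress criterion for doing so and does not say that anyone looks at the scores.
- Blinding and data access says the chat psychologist cannot see what participants submit, so a high score does not reach the clinician in contact with the patient by that path.

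**Step 5: a test case.** Take a patient whose depression score is in the most severe range at T_m8, whose weight is stable and who reports no risk eating behavior. All four criteria in Step 1 return no. The only remaining route is a researcher's discretion, with nothing in the text to prompt it.

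**The case against.** The strongest reply is that a distress route is written. Identification is by the research team or the program, either a researcher or the program can raise the alert, and the sentence listing (a) and (b) does not say these are the only grounds. On that reading the two triggers are fixed additions to a general duty to act on distress. This stands in part: a reader might infer that a very high score leads to no action, or that no questionnaire could ever raise an alert, and the text does not go that far. It leaves discretion open. It does not say what that discretion rests on.

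A second reply is that score cut-offs and contact times are operational detail that a condensed article leaves to the full protocol or the ethics file. That would answer a complaint about silence. Here the article prints the trigger list, and the list does not match the purpose given just before it.

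A third reply is that other channels narrow the gap. Intervention patients can book a chat with a supervised psychologist every other week, and the psychologist may recognise distress in conversation. Both arms keep treatment as usual and are weighed in person by the research team. These are real mitigations, but none is a stated trigger, and the chat is open to one arm only.

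A reader might also infer that controls can never meet trigger (b), because the weekly items go weekly only to the intervention group. The documents do not settle this. Trigger (b) names no data source, controls answer the same items at scheduled assessments, and both arms complete two eating questionnaires whose recall periods are not given.

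**Conclusion.** The concern holds as a mismatch between a safety rule and its stated purpose. None of the four listed alert criteria reads distress, and none of the six scheduled distress assessments is linked to an alert in the text. A patient with a very high score but stable weight and orderly eating meets no listed trigger and depends on undirected discretion.

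The conclusion rests on the article as printed and assumes that no fuller document adds a distress trigger. It does not support a count of patients missed: the documents give no prevalence of severe scores in this population, and any figure would be an assumption. Nor does it show bias in the randomised comparison, which a reader might infer from an alert system fed partly by intervention-arm monitoring. The rationale section presents monitoring and referral as part of the program under test. The change should be made because it closes a safety gap using data already collected.

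**What to change.** Keep triggers (a) and (b) and add a trigger (c): a score at or above a cut-off marking the most severe range on the depression, anxiety or stress subscale. The clinical lead sets the cut-off before the rule is used, and it is written into the protocol with a maximum time to contact. The program checks it automatically when the form is submitted, in both arms and at every assessment from T_b to T_fu12. A positive check prompts coordinator contact and then the referral that the safety section already provides. State also that a researcher may raise an alert for distress outside these triggers.

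Notify the ethics committees and the trial registry, as the article already undertakes to do for modifications. Recruitment was not complete when the article was written, so the rule could still protect enrolled and future patients. Record each alert and referral by arm so that its effect can be described.

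The cost is one programmed check on a form both arms already complete, the notifications, and extra coordinator contacts. Their number should be modest with a cut-off in the most severe range, but it cannot be worked out from the documents. No new items, visits or patients are needed. The rule is identical in both arms, so it adds no difference in procedure between them; its effect on weight regain cannot be sized from what the article gives.
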